### Outcomes

#### Primary outcomes

Our primary outcome of inappropriate management for threatened preterm labour is defined by:number of inappropriate admission decisions: admitted and delivery interval > 7 days OR not admitted and delivery interval < 7 daysandnumber of inappropriate in-utero transfer decisions/actions: in-utero transfers that occurred or were attempted > 7 days prior to delivery, and ex-utero transfers within 24 h that should have been in-utero (attempted and non-attempted)

#### Secondary outcomes

Secondary outcomes will include:All components of primary outcome individuallyMaternal clinical outcomes (e.g. new onset gestational diabetes, thromboembolic disease and confirmed sepsis)Neonatal clinical outcomes (e.g. neonatal death prior to discharge, gestational age at delivery, birthweight, days of supplemental oxygen)Process measures (days of maternal hospitalisation, steroid, tocolytic and magnesium sulphate administration, neonatal intensive-care admissions, ex-utero transfer within 24 h of delivery)Compliance to management recommendations

Information will also be collected on the number of preterm deliveries before 34, and 37 weeks, and on the use of treatments to prevent prematurity [antibiotics, cerclage (by site), progesterone]. The authors may be contacted for samples of the data collection forms.

#### Health economic outcomes

Cost-savings will be generated as a result of:Reduction in the number of inappropriate admission decisions.Reduction in the number of inappropriate in-utero transfer decisions.

#### Women’s experience study (EQUIPTT-Q)

Our key outcome is difference in VAS anxiety scores between women before and after assessment, between hospitals with and without QUIPP app in use at the time of assessment. We will also analyse difference between DCS scores after assessment, in hospitals with and without QUIPP app in use.

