#### **Hypothesis:** The implementation of the QUIPP app and management algorithm will decrease inappropriate management for TPTL

### Trial design

EQUIPTT is a cluster randomised controlled trial (incorporating a parallel group design) across 13 obstetric centres. This design was chosen as for this scale of protocol intervention (in an emergency situation), it would be challenging to randomise at participant level, affecting uptake and generalisability of the findings, and individual clinicians cannot be randomised to varying decision-making with individual patients.

The pragmatic approach was taken to introduce the QUIPP app to entire hospital antenatal units, as standard practice for all clinicians, and all affected pregnancies. Using this parallel cluster studies have the added value of limiting the time-bias which occurs with a stepped wedge design. Also, unlike in a crossover design, the intervention does not need to be retracted from the cluster, avoiding contamination bias. Individuals within a cluster tend to have more similar outcomes than across clusters. The similarity in the outcomes of individuals within a cluster within a time period is typically measured by the within-cluster within-period intra-cluster correlation coefficient. If this is not factored into the power calculation and analysis, the effectiveness of the intervention may be exaggerated [18].

All 13 centres will provide data related to the principal outcome under their current practice in a six-week pre-intervention data collection period. Following randomisation, the centres will use intervention (using the QUiPP app) or control (routine management) for a nine-month analysis period. In the final phase of the trial, the intervention will be introduced in the 6 control units. Following this, data will be collected for a further six weeks across all 13 sites, in order to equally incentivise all sites to participate. The QUIPP app approach will be adopted as standard practice in all sites if successful. A list of the study sites is available from the authors on request.

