#### Women’s experience study (EQUIPTT-Q)

When feasible (i.e. participants identified prior to assessment and staff available to obtain consent), participants in the cluster randomised trial will be invited to complete a questionnaire booklet. This includes questions about her symptoms, anxiety levels before and after her clinical assessment, the tests she received, her options for further management and the extent to which she is content with the decisions made. Anxiety levels and decisional conflict will be ascertained by visual analogue scale (VAS), and the Decisional Conflict Scale (DCS) questions [19]. The questionnaire booklet has been designed in collaboration with the Women’s Health Academic Centre’s Preterm Birth Studies public and patient involvement (PPI) panel. Difference in VAS anxiety scores between women before and after assessment, and between hospitals with and without QUIPP app in use at the time of assessment, will be calculated (paired and independent samples t-test). Difference between DCS scores after assessment, between hospitals with and without QUIPP app in use, will also be calculated (paired and independent samples t-tests as appropriate). If the DCS and VAS data is found to be not normally distributed, non-parametric equivalent tests will be used.

A subgroup of participants (approx. 20–30) will be invited to provide a more in-depth account of their experiences during one-to-one face-to-face or telephone interviews. The interview schedule will be determined following interim analysis of the data and free text box comments. The Framework approach [20] will be used to analyse the qualitative data obtained from the interviews. This method of qualitative data analysis is suitable for use with the anticipated findings from this study. Data will be analysed using NVivo software.

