### Implementing the QUiPP app intervention

In each phase, each cluster will recruit consecutive women with singleton or twin pregnancies presenting between 23^+ 0^ and 34^+ 6^ weeks presenting with symptoms of preterm labour. Eligible participants will be identified at labour ward and day assessment triage by the direct care team and local research support teams. Inclusion and exclusion criteria are defined above.

All sites will receive training on the use of the QUIPP App and management guidance prior to its introduction, and periodically throughout the trial at peaks of staff turnover. This training will be delivered by the trial team at different times and locations to suit each site, for example, at departmental audit meetings and staff induction. Training will be delivered via clinical vignettes which provide opportunity for the clinicians to use the app in a training environment. Aide-memoires such as lanyards and pens are provided to each site to encourage use of the app. The doctor/midwife assessing the woman inputs the gestation, previous history of late miscarriage or preterm birth, quantitative fetal fibronectin value and/or ultrasonic cervical length into the app and the app provides % risk of delivery within 1/2/4 weeks and before 30/34/37 weeks. The exact thresholds for admission or treatment are gestation-dependent and may need to be tailored to individual circumstances. However as a recommendation, our guidance will suggest a 5% risk of delivery within 7 days as threshold for antenatal corticosteroid administration, admission, and/or in-utero transfer. Ultimately however the management decisions following the knowledge provided by the QUIPP app will remain the clinicians’ responsibility. A feedback option is available on the app to directly contact the trial team with specific non-clinical queries. Incentives and competitions will also aim to increase recruitment for the qualitative recruitment.

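### EQUIPTT-Q compares hospitals by whether the app was running at assessment rather than by allocated arm, so women from outside the randomised nine months can enter the key comparison

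*Protocol article*

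**What the plan says.** The grouping rule appears twice in the protocol article. Under Outcomes, Women's experience study (EQUIPTT-Q), the key outcome is the "difference in VAS anxiety scores between women before and after assessment, between hospitals with and without QUIPP app in use at the time of assessment". Under Data analysis, in the section of the same name, the VAS difference "between hospitals with and without QUIPP app in use at the time of assessment, will be calculated" by paired and independent-samples t-tests, and the decisional conflict score is handled in the same way. Neither section mentions allocated arm or trial phase.

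Trial design sets out three phases:
- six weeks of current practice at all 13 centres;
- nine months with centres on intervention or control as randomised;
- introduction of the app in the 6 control units, after which "Following this, data will be collected for a further six weeks across all 13 sites, in order to equally incentivise all sites to participate".

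On who is approached, the analysis section says that, when feasible, "participants in the cluster randomised trial will be invited to complete a questionnaire booklet". Implementing the QUiPP app intervention says "In each phase, each cluster will recruit consecutive women". The main trial, under its own heading in Data analysis, is analysed by intention to treat, on the planned intervention.

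**The concern.** In a parallel cluster trial, arm and app status normally coincide. Here they do not, because every hospital moves from no app to app at some point. Grouping by status on the day puts roll-out women at control hospitals in the group with the app, and would put any baseline women at intervention hospitals in the group without it. The same hospital can then stand on both sides, and the group with the app falls later in calendar time on average.

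Only the nine-month period is a randomised, concurrent comparison. Any change over time in how anxiety shifts across an assessment, or in which women are asked to complete a booklet, would be read as an effect of the app. The protocol plans incentives and competitions to raise recruitment to the questionnaire study, so the mix of respondents could change. Trial design itself cites less time bias than a stepped wedge as a reason for the parallel layout. Pooling by current app status gives part of that advantage away, and the stated t-tests have no term to recover it.

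**Working it through.** **The plan's own figure.** Sample size gives 272 women for 90% power at two-sided 0.05 to detect a 10% difference in mean VAS. No SD is stated, so 272 cannot be reproduced from the stated inputs. Solving backwards at the individual level with 136 per group: d = (1.960 + 1.282) × √(2/136) = 0.393. That implies an SD of about 10/0.393 = 25.4 if 10% means 10 points on a 0-100 scale. Only the power check below uses this.

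**Inputs for exposure.** From Trial design: 6 weeks, nine months, 6 weeks; 13 sites, 6 of them control. Seven app sites follow from 13 − 6, and agree with the NICU ratios under Randomisation (4+3+0 against 3+2+1). Assumptions: nine months is 39 weeks, booklets accrue evenly per site-week, and there is no gap at roll-out.

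**Site-weeks by app status**
- Randomised period: with app 7 × 39 = 273; without 6 × 39 = 234; together 507.
- Baseline: 13 × 6 = 78, all without app, of which 7 × 6 = 42 are at intervention hospitals.
- Roll-out: 13 × 6 = 78, all with app, of which 6 × 6 = 36 are at control hospitals.

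| Phases that enter | With app | Without app | Outside the randomised period | Counted opposite to arm |
|---|---|---|---|---|
| Nine months only | 273 | 234 | 0 | 0 |
| Plus roll-out | 351 | 234 | 78/585 = 13.3% | 36/585 = 6.2% |
| Plus roll-out and baseline | 351 | 312 | 156/663 = 23.5% | 78/663 = 11.8% |

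**Calendar gap.** The phase midpoints are weeks 3, 25.5 and 48, so each outer phase lies 22.5 weeks from the middle.
- Roll-out only: 22.5 × 78/351 = 5.0 weeks.
- All phases: 5.0 + 22.5 × 78/312 = 5.0 + 5.6 = 10.6 weeks.

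**Bias from a drift D in VAS change that is unrelated to the app** = D × gap / span. The span is 51 weeks if D runs over the whole trial, or 48 − 3 = 45 weeks if D runs from first to last midpoint. With D = 5 points:
- Roll-out only: 5 × 5.0/51 = 0.49, or 5 × 5.0/45 = 0.56.
- All phases: 5 × 10.625/51 = 1.04, or 5 × 10.625/45 = 1.18.

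Over 51 weeks, drifts of 2 and 10 points give 0.2 and 1.0 (roll-out only), or 0.4 and 2.1 (all phases). The target difference is 10 points.

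**Cost of keeping only the nine months.** Of 300 booklets spread evenly over all phases, 300 × 507/663 = 229 remain. Power at d = 0.393 is Φ(0.393 × √(229/4) − 1.96) = Φ(1.01), about 84%. If booklets come from the nine months and roll-out only, 300 × 507/585 = 260 remain. Both are below 272. The power figure is individual-level, with no allowance for clustering.

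**The case against.** The strongest reply is that the exposure is possible but not stated. No section says booklets are collected outside the nine months, which is the only stretch called the analysis period. If they are confined to it, app status and arm coincide apart from late or failed uptake, and nothing is wrong. The sentence on recruiting in each phase describes the main trial, and EQUIPTT-Q invitations are made only when feasible. This is why the point is about what the rule admits. A reader might infer that the comparison is in fact a before-after one, and the text does not show that. It remains true that the qualifier about the time of assessment would be largely redundant if only the nine months counted, and that no section excludes roll-out women.

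Second, Trial design describes the baseline collection as data on the principal outcome, and neither VAS anxiety nor decisional conflict is that. This stands: the baseline route is the weaker one, and the 24% should not be quoted without the 13%.

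Third, a reader might infer a contradiction with intention to treat. The documents do not support this. That sentence sits under the cluster-trial heading, and EQUIPTT-Q has its own. The contrast is also between hospitals, not between women for whom the app was or was not used. It departs from the main trial's principle without contradicting it.

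Fourth, the drift is assumed, and it would have to occur in the within-woman change. No section gives evidence of one. This stands, and limits the claim about size.

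Fifth, an article may leave a substudy's analysis set to a fuller document. That would excuse silence, but here the grouping rule is stated twice, and it is not the randomised one.

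**Conclusion.** The concern holds in a limited form. As written, the rule lets roll-out women, and less certainly baseline women, into an unadjusted comparison, which would then be partly non-randomised and non-concurrent. Under even accrual, 39 weeks and seven app sites, the non-randomised share is 13% with roll-out only and 24% with both outer phases. A 5-point drift on a 0-100 scale, both assumed, would move the contrast by about 0.5 to 1.2 points against a 10-point target. The likely bias is therefore modest, and zero if booklets are collected only in the nine months and app use follows allocation. The fault is a definition that does not protect the randomised comparison, in a substudy rather than the primary outcome. It is worth correcting because the correction is simple.

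**What to change.** In both EQUIPTT-Q sections (Data analysis and Outcomes), define the key comparison as hospitals allocated to intervention versus hospitals allocated to control, among women assessed during the nine-month analysis period. Apply this to VAS and decisional conflict alike. Count the 272 required and the 300 targeted within that period. Report any booklets from the other phases descriptively, or in a secondary analysis adjusted for period.

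The cost is that booklets from the other phases no longer count towards the main comparison. If they make up about 24% of 300, about 229 remain, below the stated 272; either recruitment within the nine months must make up the difference or the stated 90% power must be restated. If EQUIPTT-Q already runs only in the nine months, the change is one of wording and loses no data.

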## Discussion

Management of TPTL has represented a clinical conundrum for decades. Intervention “just-in-case” results in many unnecessary admissions, women being transferred out of their local hospital unnecessarily and most women receiving unnecessary drugs, such as steroids and tocolytics. It also prevents appropriate transfers as neonatal cots are blocked unnecessarily, resulting in more dangerous ex-utero transfers. One reason for the current trend for over-treatment of TPTL is concern that the false-negatives any triage system entails. This study will determine the risks and benefits of limiting management and treatment to those most at risk of delivery.

The exact thresholds for admission or treatment are gestation-dependent, may need to be tailored to individual circumstances and will remain the clinicians’ responsibility. As a recommendation, our guidance will suggest a 5% risk of delivery within seven days as threshold for antenatal corticosteroid administration, admission, and/or in-utero transfer. A 5% threshold is equivalent to an odds of 5:95 which is 1:19. This estimates the harm of a missed imminent delivery (a false negative) is 19 times as great as the harm of overtreatment (a false positive). It was found to be an acceptable threshold for intervention in our Delphi survey of preterm birth specialists. In the context of national guidance which advocated more intervention and disregarded the risk of harm this incurs to the majority [2], this study’s comprehensive evaluation of the true clinical impact of the QuiPP app will determine and justify an appropriate threshold for TPTL intervention for the first time.

If, as we hypothesise, the QUIPP app improves selection of the appropriate women for admission and transfer, it will ensure that therapies known to reduce risk of preterm neonatal morbidities are offered to those who need them and reduce the associated maternal and fetal risks to women who do not. Conversely if a treat-all policy is justified, we can help define resource use and clinical need to inform policy makers. Beyond obstetrics, evaluating the impact of an app in an emergency setting, and our emphasis on balancing harms of over-treatment as well as under-treatment, make EQUIPTT a valuable contribution to translational medicine.

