### Sample size

For inappropriate admission decisions, a total sample size of 580, approximately 50 recruits per site, was calculated. Data from our group’s ongoing prospective observational study into the ability of qfFN to predict preterm birth in symptomatic women (PETRA REC Ref. 14/LO/1988) has allowed us to estimate the likely treatment effect for the intervention reducing inappropriate admissions from 25 to 10% and intra-class correlation 0.030. Based on 13 clusters this treatment effect requires approximately 580 for 80% power. We are aware that a larger number of centres would also be preferable, but believe 13 is adequate and at the limit of what is currently feasible.

For our qualitative questionnaires, we have estimated a target recruitment of 300 participants, 25 recruits per site, allowing for non-compliance and data collection errors. Based on previous research involving visual analogue scale (VAS) scores [19], a total sample size of 272 was required at standard levels of significance (alpha = 0.05 two-sided) to achieve 90% power to detect a 10% difference in mean VAS scores between hospitals with and without the intervention.

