### Data analysis

#### Cluster randomised trial

Data analysis will follow the intention to treat principle, according to the planned intervention. Data will be analysed using Stata software Version 14 or later (StataCorp, College Station, Texas) to estimate the size and test for statistical significance of any effects of the intervention on primary and secondary, and analysis will be supervised by the trial statistician, [name]. A per protocol analysis will also be performed, excluding those who are incidentally admitted or treated for reasons unrelated to preterm labour. Treatment effects for binary endpoints will be expressed as risk ratios (relative risk) with 95% CIs, using binomial regression and adjusting for variables used in the minimization process. Risk differences will also be calculated for the primary endpoint. The analysis model will include a random effect for clustering and adjusted standard errors for clustering. Adjustments will also need to be made for differences between cluster populations, such as ethnicity and maternal age. Our primary outcome of inappropriate decisions will be measured per 1000 deliveries.

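### The 5% guidance is read as a 19:1 harm ratio but the primary outcome counts both errors equally, so it could improve while harm on that scale rises if women diverted from admission average above 5% seven-day risk

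*Protocol article*

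**What the plan says.** **Threshold and its meaning.** Under Implementing the QUiPP app intervention, "our guidance will suggest a 5% risk of delivery within 7 days as threshold" for steroids, admission and transfer. The Discussion repeats this and adds "A 5% threshold is equivalent to an odds of 5:95 which is 1:19", from which it concludes that "the harm of a missed imminent delivery (a false negative) is 19 times as great as the harm of overtreatment". The Background and the Discussion give earlier published work and a Delphi survey as the sources of the 5%. The 19:1 ratio is derived from the 5% and is not its origin.

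**Primary outcome.** Under Primary outcomes, an admission decision is inappropriate in either of two ways: the woman was admitted and delivered more than 7 days later, or she was not admitted and delivered in under 7 days. The transfer part likewise pools unneeded in-utero transfers with ex-utero transfers that should have been in-utero. The Cluster randomised trial section plans risk ratios and adds: "Our primary outcome of inappropriate decisions will be measured per 1000 deliveries". No weights appear, and no limit on missed deliveries is attached to the primary result.

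**Planned effect.** The Sample size section assumes "reducing inappropriate admissions from 25 to 10" percent, an intra-class correlation of 0.030, 13 clusters and about 580 women. It does not split the 25% or the 10% between the two kinds of error.

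**Reporting of parts.** Secondary outcomes lists each component of the primary outcome separately, along with neonatal outcomes and compliance with the recommendations.

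**The concern.** The decision guidance is explained on one scale (19:1) and judged on another (1:1). An unweighted count of errors is smallest when women are admitted only above a 50% risk, because that is where the two errors become equally likely. A woman at exactly 5% risk who is admitted will be scored as an inappropriate decision 95 times in 100; sent home, she will be scored so 5 times in 100. The primary count therefore rewards fewer admissions over a much wider range of risk than the protocol's own reading of harm would accept.

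At stake is how a positive result is interpreted. The trial says that it will balance over-treatment against under-treatment and help to justify a threshold. A significant fall in the primary count could come from better triage, or from admitting fewer women with some extra missed deliveries. The count alone cannot tell these apart.

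**Working it through.** **1. The protocol's own figure.** (1 − 0.05)/0.05 = 19. The 1:19 odds are reproduced exactly.

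**2. The two scales.** Let FP be women admitted who deliver after 7 days and FN be women not admitted who deliver within 7 days, both per 100 women.
- Primary count (admission part) = FP + FN
- Harm on the stated scale = FP + 19 × FN

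**3. When they disagree.** Suppose the app moves m women per 100 from admitted to not admitted, and a share r of them deliver within 7 days. FP falls by m(1 − r) and FN rises by m·r.
- Change in count = −m(1 − 2r), a fall whenever r < 50%
- Change in harm = −m(1 − r) + 19·m·r = m(20r − 1), a fall only when r < 5%

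For r between 5% and 50% the count improves and harm worsens.

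**4. Size at the planned effect.** The count falls by 15 points. If FN rises by y points, FP must fall by 15 + y, so the change in harm = 19y − (15 + y) = 18y − 15. This is zero at y = 15/18 = 0.83 points, and 290 × 0.0083 = 2.4 women (290 = 580/2). The result does not depend on the unstated FP/FN split. For a general weight w, break-even is 15/(w − 1).

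In terms of r, with m = 15/(1 − 2r):

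| r | women moved per 100 | rise in FN | fall in FP | change in harm per 100 |
|---|---|---|---|---|
| 1% | 15.31 | 0.15 | 15.15 | −12.2 |
| 3% | 15.96 | 0.48 | 15.48 | −6.4 |
| 5% | 16.67 | 0.83 | 15.83 | 0 |
| 8% | 17.86 | 1.43 | 16.43 | +10.7 |
| 10% | 18.75 | 1.88 | 16.88 | +18.8 |

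**5. Illustration (assumed split).** Control: 24.5% FP and 0.5% FN, harm 24.5 + 9.5 = 34.0. App: 8.0% FP and 2.0% FN, harm 8.0 + 38.0 = 46.0, a rise of 35%. The primary outcome meanwhile shows the full planned benefit (10/25 = 0.40). Here 1.5 of the 18.0 diverted women per 100 deliver within 7 days, so r = 8.3%. The example therefore presupposes an app that is miscalibrated or not followed.

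**6. Would the separate component show it?** Assume two-sided 5% significance (not stated for the primary outcome), 290 women per arm, and the planned correlation of 0.030 applied to missed deliveries. With 580/13 = 44.6 women per cluster, the design effect is 1 + 43.6 × 0.030 = 2.31.
- FN 0.5% v 2.0%: power about 37% ignoring clustering, about 19% allowing for it
- FN 1% v 2%: about 17% and 10%

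The same sample gives about 81.5% power for 25% v 10% (6 v 7 clusters, t reference on 11 degrees of freedom), so the sample size itself is not in dispute.

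**The case against.** The strongest reply is that the break-even is the 5% rule in another form: harm rises only if the women diverted average more than 5% risk. The guidance diverts women below 5%, and the Background says that most receive a risk under 1%. With a calibrated app that is followed, both scales fall. This stands, and it limits the point to a conditional one. It does not remove it, because the trial objectives include external validation of the model and clinicians keep discretion to depart from the guidance.

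Other parts of the reply also stand:
- The components, neonatal outcomes and compliance are already to be reported, and a data monitoring committee reviews adverse neonatal outcomes. What is lacking is a common scale for reading the components together, and the missed-delivery component has little power on its own.
- The analysis plan is not shown and may contain a weighted analysis. The point therefore rests on the two scales that this document itself sets down.
- The 19:1 ratio interprets a provisional guide, so it should not be treated as a fixed truth.

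A reader might infer more than the document supports:
- **That the 5% threshold is founded on 19:1.** The derivation runs the other way.
- **That the app is likely to raise harm.** Nothing here predicts that.
- **That admitting nobody would meet the 10% target.** On the admission part such a policy scores the 7-day delivery rate, which is not given. The transfer part also penalises missed cases, and no arm tests the policy.

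**Conclusion.** The point holds in conditional form. The protocol states a 19:1 valuation of the two errors and then counts them 1:1, with no combined analysis on the stated scale. If diverted women deliver within 7 days at a rate between 5% and 50%, the primary outcome improves while harm on that scale worsens. At the planned effect this needs a rise in missed deliveries of more than 0.83 points, about 2 to 3 women per arm of 290. That figure assumes only the planned 15-point fall and the 19:1 ratio. The illustrative harm totals and the power figures rest on assumed missed-delivery rates.

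This is a worthwhile improvement to the interpretation of the trial. It does not invalidate the primary outcome, and it takes no position on which clinical threshold is right.

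**What to change.** Keep the primary count as it is. Beside it, pre-specify:

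1. **A weighted (net-benefit) analysis of admission decisions.** Each woman scores 19 if not admitted and delivered within 7 days, 1 if admitted and delivered after 7 days, and 0 otherwise. Because the score is not binary, the planned binomial model does not fit it. Use a cluster-adjusted model for the mean score and report the difference with its 95% confidence interval.
2. **A sensitivity range of weights,** fixed in advance, since 19:1 comes from a provisional threshold.
3. **Both directions of error with confidence intervals next to the primary result.** The components are already planned as secondary outcomes, so this concerns placement only.
4. **A statement on interpretation.** A fall in the primary count is to be read as improved management only in light of the weighted estimate and its interval. Do not make the sign of the weighted estimate a veto: with break-even at 2 to 3 women per arm and 13 clusters, chance alone could reverse it.

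The cost is analysis-plan wording and one further model on data already collected; the sample size does not change. The weighted estimate will be imprecise because missed deliveries are expected to be rare, and the overall conclusion may be less favourable than the count alone would suggest.
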